**Methods:**

The study is designed as a two-armed cluster randomized controlled trial with a late intervention control group. The hospital units are the clusters of randomization and participants are nurses and aides. An evidence-based multi-component intervention was designed combining participatory ergonomics, case management and health promotion. Both the intervention and the control groups receive occupational health care as usual. Data are collected at baseline, and after six and 12 months. The primary outcomes are prevalence of MSP and incidence and duration of sickness absence due to MSP. Secondary outcomes are work role functioning and organizational preventive culture. The intervention process will be assessed through quantitative indicators of recruitment, context, reach, dose supplied, dose received, fidelity and satisfaction, and qualitative approaches including discussion groups of participants and experts. The economic evaluation will include cost-effectiveness and cost-utility, calculated from the societal and the National Health System perspectives.

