The INTEVAL_Spain is an evidence-based intervention and consists of three components: participatory ergonomics (primary prevention of occupational risk factors), case management (secondary and tertiary prevention) and promotion of healthy lifestyles at work. There is an increasing concern on the so-called participatory ergonomics programs because they are both multi-factorial and participatory [18] and are defined as interventions in the workplace in which the relevant company agents actively participate with the aims to identify and act over the determinants of MSDs [19, 20]. Participatory ergonomics programs have been tested in Spanish companies with promising results [21, 22]. There is scientific evidence that the management of musculoskeletal symptoms through a tailored approach could be more efficient if individuals are stratified according to certain prognostic profiles in the initial stages of the disorder and after treatment [23, 24]. At tertiary prevention, the available scientific evidence suggests that case management can reduce the duration of sickness absence, musculoskeletal symptoms and disability, and improve work continuity [25–27]. Integrating activities on healthy lifestyles at work is also an important component of occupational health programs to reduce MSP [28], so different strategies promoting workers’ physical activity, emotional wellbeing and healthy diet [29–32] were also included. As for healthcare workers, promoting healthy lifestyles should be a priority because of its double impact on their own health and that of patients, encouraging these lifestyles within the general population. In addition, the World Health Organization considers workplace as one of the best contexts for the prevention and control of non-communicable diseases [33].

This paper presents the design of a study that evaluates the multifaceted INTEVAL_Spain intervention in the workplace in nursing staff from two tertiary hospitals to prevent and manage MSP and its associated sickness absence. We hypothesize that this intervention will be effective in terms of reducing the prevalence of MSP and will also reduce the incidence of associated sickness absence and the time to return to work in the intervention group at the end of the study, compared to the control non-intervention group. In addition, a process evaluation of the intervention and its association with the impact on MSP, and an economic evaluation will be carried out.

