### Eligibility criteria

The inclusion criteria are nursing staff (nurses and aides), including employees on sickness absence, who voluntarily accept to participate. Workers with a temporal contract during a short period, working in several units and on sabbatical leave are excluded.

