### Intervention

The intervention covers the three levels of prevention (primary, secondary and tertiary prevention), lasts for 1 year and is implemented to the control group thereafter.

For primary prevention of occupational risk factors, a standardized procedure of participatory ergonomics named ERGOPAR, developed and previously piloted in Spain is used [39]. A working group (ERGO group) is organized for each hospital unit, including a specialist in ergonomics, the unit supervisor/s, one referent worker for each shift (morning, afternoon and two night shifts) and one workers’ union representative. This ERGO group is responsible for the development and implementation of the intervention, and receive basic training in ergonomics and participatory methods. The intervention begins with the diagnostic phase, with the distribution of a previously validated self-completed questionnaire in which data on MSP and exposure to musculoskeletal risk factors at work are collected using specific risk assessment. This information is then analyzed and discussed by the ERGO group and a prioritized list of risk factors is developed. The next step is the treatment phase, in which the information collected in the questionnaires is shared and discussed with coworkers in the so-called prevention circles. These circles propose a prioritized list of preventive measures aimed to avoid or reduce the identified ergonomic risk factors. This list may include structural, technical, organizational, training and/or information measures for improvement, and workplace modifications. The OHS coordinates the implementation of these measures along with the corresponding department managers. Based on the previous available experience with the ERGOPAR method [22], the time required to complete all phases of the intervention in each work unit has been estimated from six to 12 months.

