#### Sickness absence

Data on episodes and duration of sickness absence due to a musculoskeletal condition (MSP or MSDs) are collected from the company registries and the OHS during the study period and 1 year before the intervention.

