### Data analysis

Statistical analyses adapted for cluster-randomized controlled trials will be conducted. Descriptive analyses of the participants’ characteristics and comparisons between the intervention and control clusters will be performed. The generalized estimation equations (GEE) procedure will be used for the analysis of the MSP, work functioning and organizational preventive culture comparing the difference from the baseline to the 12-month follow-up of the intervention group, with the difference from the baseline to the 12-month follow-up of the control group. The models will be adjusted by the cluster design and by the potential confounders. The incidence of sickness absence will be analyzed through a logistic regression model, taking as a reference the episodes started the year before the intervention and the control group. A Cox proportional hazard model will estimate the hazard ratio of returning to work earlier after the intervention in the intervention group compared to the control group.

Statistical analyses will be performed with STATA 13 (StataCorp, 2013. Stata Statistical Software: Release 13. College Station, TX: StataCorp LP).

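### The return-to-work Cox model, the only comparison stated for the primary duration outcome, is conditional on going absent, which the intervention is meant to change, so its hazard ratio is not a randomised comparison

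*Protocol article*

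**What the plan says.** The abstract lists the primary outcomes: "The primary outcomes are prevalence of MSP and incidence and duration of sickness absence due to MSP". The Background states the matching hypothesis, that the intervention "will also reduce the incidence of associated sickness absence and the time to return to work in the intervention group". Fewer absences and shorter absences are therefore both expected.

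The Data analysis section treats the two separately. For incidence: "The incidence of sickness absence will be analyzed through a logistic regression model, taking as a reference the episodes started the year before". For duration: "A Cox proportional hazard model will estimate the hazard ratio of returning to work earlier after the intervention in the intervention group", compared with the control group. It states no other between-arm analysis of duration. The Economic evaluation section uses sick leave only to cost lost production.

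On the data, the Sickness absence section says: "Data on episodes and duration of sickness absence due to a musculoskeletal condition (MSP or MSDs) are collected from the company registries" and from the occupational health service, for the study period and the year before. The Eligibility criteria admit nursing staff "including employees on sickness absence". The Intervention section says that the programme "lasts for 1 year and is implemented to the control group thereafter".

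**The concern.** Randomising units makes the workers in the two arms comparable. It does not make comparable the subsets of workers who later go absent. Time to return exists only for that subset, and membership of it is itself a hypothesised effect of treatment. The Intervention section gives a route for this: case management can include job adjustments that help a worker stay at work, so an absence that would have occurred in a control unit may not occur in an intervention unit.

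If the prevented episodes differ in severity from those that remain, the arms contribute different mixes to the Cox model, and the hazard ratio moves even when no individual episode changes length. Adjusting for unit or for baseline confounders does not undo selection that takes place after randomisation. The stake is the reading of a primary outcome: a real benefit could look like slower return, or prevention of long episodes could be credited as faster recovery.

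**Working it through.** **The plan's own figures.** The only sample size figure, 164 workers (82 per group), is for pain prevalence. It reproduces as a two-sided comparison of 80% with 60% at alpha 0.05 and power 0.80. It does not bear on absence. The protocol gives no absence rate, episode length, hazard ratio or event count, so every input below is an assumption.

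**Assumptions.** Each worker has at most one episode in the year, either short (exponential, mean 10 days) or long (exponential, mean 60 days). pS and pL are the control probabilities of each type; fS and fL are the fractions that still occur under intervention. Then:

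- days per worker = 10·pS·fS + 60·pL·fL
- mean days per episode = days per worker ÷ (pS·fS + pL·fL)

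**A hand check.** Suppose 60% of control episodes are short and 40% long. The control mean is 0.6 × 10 + 0.4 × 60 = 30.0 days. Prevent half the short ones and change nothing else: (0.3 × 10 + 0.4 × 60) ÷ 0.7 = 27 ÷ 0.7 = 38.6 days per episode. Total days fall to 27/30, a 10% reduction. A simulated Cox model for this mix gives a hazard ratio of 0.82 (0.90 if 30% of short episodes are prevented). The mean per remaining episode rises while total absence falls.

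**Simulation over two other mixes.** There were 60,000 workers per arm, with start dates uniform over 365 days and return to work censored at year end. The Cox model was fitted only to workers with an episode. A hazard ratio above 1 means earlier return. The intervals reflect simulation error, not the precision of this trial. Days columns come from the formulas above and count each episode's full length. Recovery is unchanged in every row.

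| Control mix | Episodes prevented | Days per worker, control → intervention | Days per episode, control → intervention | Cox HR (95% interval) |
|---|---|---|---|---|
| 10% short, 10% long | none | 7.0 → 7.0 | 35.0 → 35.0 | 0.98 (0.96–1.01) |
| | 30% of short | 7.0 → 6.7 | 35.0 → 39.4 | 0.89 (0.87–0.92) |
| | 50% of short | 7.0 → 6.5 | 35.0 → 43.3 | 0.82 (0.80–0.85) |
| | 50% of long | 7.0 → 4.0 | 35.0 → 26.7 | 1.25 (1.21–1.28) |
| | 30% of both | 7.0 → 4.9 | 35.0 → 35.0 | 0.97 (0.94–1.00) |
| 15% short, 5% long | none | 4.5 → 4.5 | 22.5 → 22.5 | 1.00 (0.97–1.02) |
| | 30% of short | 4.5 → 4.05 | 22.5 → 26.1 | 0.92 (0.90–0.95) |
| | 50% of short | 4.5 → 3.75 | 22.5 → 30.0 | 0.81 (0.78–0.83) |
| | 50% of long | 4.5 → 3.0 | 22.5 → 17.1 | 1.20 (1.17–1.24) |
| | 30% of both | 4.5 → 3.15 | 22.5 → 22.5 | 0.99 (0.96–1.02) |

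**With a true recovery effect.** Prevent half the short episodes and also speed recovery within each episode type. With recovery 10% faster the hazard ratio is 0.88 and 0.87 in the two mixes; with 20% faster it is 0.96 and 0.94. Simulated days per worker fall throughout: 6.94 to 6.07 and 4.42 to 3.38 at 10%, 6.90 to 5.32 and 4.58 to 3.10 at 20%. Here the hazard ratio has the wrong sign although both hypotheses are true.

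**The case against.** **The hypothesis is about return to work.** Case management is meant to shorten absence once it occurs, and days per worker does not isolate that. This stands. Days per worker would fall with fewer episodes even if nobody returned sooner, as the rows preventing 30% of both types show, and there the Cox result near 1 is right about speed of return. Replacing the Cox model outright would change the question, so the new measure should be an addition.

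**Incidence is reported beside it.** It is also primary and has its own model, so a reader sees both results. That helps interpretation, but does not make the conditional hazard ratio a randomised contrast.

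**The direction is unknown.** A reader might infer that the model will show false harm. The documents do not support that. Nothing says short episodes are the ones prevented, and the most intensive case management goes to medium- and high-risk workers. The bias could favour the intervention or be negligible.

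**The analysis set is not defined.** The Data analysis section gives no risk set, time origin or censoring rule, and an article may leave these to the analysis plan. That the model covers absences arising after randomisation is inferred from the outcome and the hypothesis. Likewise, workers already absent are eligible, but nothing says that their ongoing episodes are pooled with new ones. That is a matter to define, not an error shown.

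**Control units under treatment.** The wording of the Cox sentence might suggest a comparison made after the intervention year, when control units are receiving the programme. The rest of the protocol does not support this reading. The Background sets the comparison at the end of the study against a control group without the intervention, the section on recruitment of participants collects absence data up to the end of the study, follow-up ends at 12 months, and control units start only after the year.

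**Conclusion.** The point holds as a limit on what the stated analysis can show. For one of the primary outcomes, the only between-arm comparison given is conditional on an event that the intervention is hypothesised to reduce. It therefore lacks the protection of randomisation, and covariate or cluster adjustment cannot supply it.

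Under the assumed mixes, and with no true change in recovery, the hazard ratio runs from about 0.81 to 1.25 according to which episodes are prevented, and stays near 1 if short and long are prevented alike. These values rest wholly on assumed rates and lengths; they show that the sign can go either way, not what this trial will find. An analysis confined to workers already absent at randomisation would escape the selection, but the protocol does not confine the Cox model to them.

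**What to change.** - **Add a randomised comparison for duration.** Use total musculoskeletal absence days per randomised worker over the 12 months after unit randomisation, with zeros included. Compare it with allowance for clustering by unit, adjusted for the unit's prior-year days. Adjust for an individual's own prior-year days only if records can be linked: the absence data are described as anonymised and the protocol does not confirm linkage.
- **Keep the Cox model for the return-to-work hypothesis.** Report it as conditional on absence, read it beside the incidence result, and do not present it as a randomised effect on duration.
- **Define its set.** Keep episodes ongoing at randomisation apart from new ones. The ongoing group is a fair comparison but will probably be small in a trial with a minimum size of 164. State the time origin, and censor at 12 months.

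**Cost.** The unit-level version is a change of analysis wording, since episodes and durations are already to be collected for the study period and the year before. Absence days are skewed and only eight units are randomised, so the interval will be wide. The measure also combines incidence with duration and cannot by itself show faster return.

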### Statistical power

The sample size estimation is based on the prevalence MSP estimated at 80% for healthcare workers [3], the impact of the intervention expecting a reduction of a 20% in the prevalence of musculoskeletal pain [53, 54], alpha values (type I error) = 0.05, statistical power = 0.80 and interclass correlation coefficient (ICC) = 0.05. Applying these criteria, we obtained a minimum sample of 164 subjects, 82 in each group. The units of the participating hospitals have a varied number of workers (20 to 60). Taking into account the sample size calculations, 8 units have been randomized.

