Our study has also potential limitations that we need to consider. There may be a participation bias, since workers with MSP could be more interested in participating, and otherwise, workers with good health could not feel the need of participating. Therefore, a sensitivity analysis comparing the sociodemographic variables of the participants and non-participants of each cluster will be carried out in order to quantify it. Moreover, there could be contamination, which could result in an underestimation of the effectiveness. However, clusters are different units located in different buildings and/or different floors, and therefore may not have much contact between them. Also, as it is a specific population (nurses and aides of public hospitals), the external validity of the results concerning the working population may be limited. Finally, questionnaires are anonymous and an identifier is not available. The research team made this decision to encourage participation and make sure that participants were feeling comfortable with the study, since the questionnaires were self-completed in the workplace and included some personal questions, as well as questions about the relationship with the supervisors. However, we are aware that this decision could limit the statistical power and entail an underestimation of the results.

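### The 82 per group is a single-time-point, unclustered number, so the stated 80% power is not supported for the planned between-arm comparison of change on unlinked questionnaires

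*Protocol article*

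**What the plan says.** The Statistical power section lists its inputs: "the prevalence MSP estimated at 80% for healthcare workers", "expecting a reduction of a 20% in the prevalence of musculoskeletal pain", "alpha values (type I error) = 0.05", "statistical power = 0.80" and "interclass correlation coefficient (ICC) = 0.05". It concludes: "Applying these criteria, we obtained a minimum sample of 164 subjects, 82 in each group". It adds that units hold 20 to 60 workers and that 8 units were randomised.

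The Data analysis section fixes the MSP analysis as GEE, adjusted for the cluster design and for confounders. Its contrast sets one arm's change against the other's: "comparing the difference from the baseline to the 12-month follow-up of the intervention group, with the difference from the baseline to the 12-month follow-up of" (quotation cut before it names the comparison arm). No link function is named. MSP prevalence is one of the primary outcomes (Abstract, Methods).

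The Recruitment of participants section says the questionnaires are anonymous. The Methodological considerations section says "questionnaires are anonymous and an identifier is not available", and concedes that this choice may reduce power.

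**The concern.** The sample size and the analysis are both stated, and they do not describe the same comparison. The 82 compares two sampled prevalences once. The planned contrast is a difference of two changes, built from four sampled prevalences. Baseline data normally pay for their extra sampling variance through the pairing of each person's answers, and without an identifier the model cannot make that pairing directly. The ICC is listed as an input but leaves no trace in the result.

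At stake is how a null result on a primary outcome is read. A reader who takes the power section at face value would treat a null arm-by-time effect as coming from a trial with 80% power to detect a 20-point fall.

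**Working it through.** **1. Where the 82 comes from.** Two independent proportions, 0.80 v 0.60 (mean 0.70), two-sided 0.05, power 0.80, pooled variance under the null:

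n = [1.96 × √(2 × 0.70 × 0.30) + 0.8416 × √(0.16 + 0.24)]² / 0.20² = 81.2, rounded up to 82.

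Other readings miss it: unpooled variance 79, continuity correction 91, one-sided 64, relative reduction (80% v 64%) 123. So the reduction was taken as 20 percentage points, at one time point, with no design effect.

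**2. The single-time comparison at 82 per arm.**
- No clustering: SE = √(0.40/82) = 0.0698; power = Φ(0.20/0.0698 − 1.96) = 82% (80.4% with the pooled null variance).
- With the stated ICC of 0.05 and 4 units per arm: variance = 0.95 × 0.40/82 + 0.05 × 0.40/4 = 0.00463 + 0.00500 = 0.00963; SE = 0.0982; power about 53%.

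The unapplied ICC alone therefore takes the single-time comparison from about 80% to about 53%.

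**3. The planned contrast, without clustering.** Control 80% to 80%, intervention 80% to 60%, waves independent. The four variances sum to 0.16 + 0.16 + 0.16 + 0.24 = 0.72.
- SE = √(0.72/82) = 0.0937; power = Φ(0.20/0.0937 − 1.96) = 57% (simulation with 200,000 replicates: 57.1%).
- n for 80% power = (1.96 + 0.8416)² × 0.72/0.04 = 141.3, that is 142 per arm per wave.

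**4. The planned contrast, with clustering.** Let ρ be the within-worker correlation between waves, assuming the same workers answer both, and CAC the correlation of a unit's effect between waves. With ICC 0.05 and 4 units per arm:

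variance = 0.95 × [0.72 − 2ρ(0.16 + √(0.16 × 0.24))]/82 + 0.05 × (1 − CAC) × 0.72/4

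Here 2 × (0.16 + √0.0384) = 0.712.

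| ρ | Bracket | Power, CAC 1 | Power, CAC 0.8 |
|---|---|---|---|
| 0 (independent waves) | 0.720 | 59% | 51% |
| 0.3 | 0.506 | 74% | 63% |
| 0.45 | 0.400 | 84% | 70% |

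These use a normal reference. With t on 6 df (8 units minus 2), the ρ = 0 row becomes 45% and 39%, and the ρ = 0.45 row 69% and 55%. The rows with ρ above 0 also need a standard error that captures the within-worker correlation through the units.

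**5. Break-even.** The change contrast matches the unclustered single-time variance when 0.72 − 0.712ρ = 0.40, so ρ = 0.45 with complete overlap of respondents.

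The document gives none of ρ, CAC, the overlap or the 4:4 split of units; they are assumptions, shown as ranges.

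**The case against.** The strongest counter-argument concerns attribution. A reader might infer from step 3 that choosing the change contrast costs about 25 points of power (82% to 57%), or that 57% is the trial's power. The document supports neither. That drop holds only with no clustering, and the plan states an ICC of 0.05. Under that ICC the single-time comparison is already at about 53%, and the change contrast with independent waves gives 51–59%, because stable unit effects cancel in a difference of changes. Most of the shortfall is thus shared with the unapplied ICC. This stands.

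Independent waves are also not quite the design described. The Recruitment of participants section describes workers who consent, complete the baseline questionnaire and are followed up, and the Process evaluation section measures reach among those who consented. That is a cohort with unlinked answers, so many respondents will answer twice. A unit-level robust variance can recover part of the correlation without an identifier, though with 8 units it is unreliable. This stands too, and it is why the result must be a range.

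The 164 is called a minimum, and 8 units of 20 to 60 hold 160 to 480 workers. At 120 or 160 respondents per arm per wave, the step 3 calculation gives 73% or 85%. So these figures judge the printed minimum; they do not show that the trial as recruited lacks power.

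Finally, the authors concede that anonymity may limit power. The concession is not quantified and does not reach the power section, so it softens the criticism without answering it.

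**Conclusion.** The concern holds in this form: the 82 per group was calculated for a different comparison from the one planned, with neither the stated ICC nor a baseline wave in it, so the 80% power at 164 subjects is not supported for the MSP analysis. At 82 per arm per wave a defensible statement is 51–59% if the waves are independent, 63–74% at a within-worker correlation of 0.3, and 70–84% at 0.45 (55–69% with t on 6 df).

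Within that grid, 80% is reached only with a normal reference, full respondent overlap, stable unit effects and a within-worker correlation well above 0.3. The plan states none of these.

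The figures rest on an absolute 20-point reduction, baseline prevalence of 80% in both arms, an unchanged control arm, 4 units per arm and a risk-difference scale. On a log-odds scale, unclustered with independent waves, power is about 46% rather than 57%. The spread across these assumptions is why no single replacement figure is justified.

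**What to change.** In Statistical power, replace the present calculation with one for the arm-by-time contrast in Data analysis. Apply the ICC of 0.05 and the 8 units. State the assumed between-wave unit correlation, within-worker correlation, effect scale and reference distribution. Then report either the power at 82 per arm per wave as a range over those assumptions, or the detectable difference at the number of respondents obtained. Remove the implication that 164 subjects give 80% power for the planned analysis, and do not print 57% as the replacement. One recalculation deals with both the contrast and the ICC.

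The cost is that recalculation, one or two reworded sentences and a less favourable stated power. Recruitment and conduct are unaffected.

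### The stated 82 per group is the individually randomised sample size: the ICC of 0.05 listed among its inputs is not reflected in it, so the claim of 80% power at that ICC is wrong as written

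*Protocol article*

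**What the plan says.** All the inputs stand in the Statistical power section of the protocol article:

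- Prevalence: "The sample size estimation is based on the prevalence MSP estimated at 80% for healthcare workers".
- Effect: "expecting a reduction of a 20% in the prevalence of musculoskeletal pain". The text does not say whether this is absolute or relative.
- Error rates and clustering: "alpha values (type I error) = 0.05", then "statistical power = 0.80 and interclass correlation coefficient (ICC) = 0.05".
- Result: "Applying these criteria, we obtained a minimum sample of 164 subjects, 82 in each group".
- Number of clusters: "Taking into account the sample size calculations, 8 units have been randomized". The same section puts unit size at 20 to 60 workers.

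Two other sections bear on the point. Data analysis plans GEE models, adjusted for the cluster design, that compare the change from baseline to 12 months between arms. Randomization describes simple randomisation stratified by centre, which does not fix a four-to-four split.

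**The concern.** The ICC is presented as one of the criteria applied to reach 82 per group. Whole hospital units of 20 or more workers are randomised, so an ICC of 0.05 should roughly double the individually randomised number or more. The stated number looks too small to contain any such inflation, and it is also the number used to justify randomising eight units.

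MSP prevalence is a primary outcome and the only one with a sample size calculation. The planned analysis will allow for clustering, so any missing inflation will show up as wider confidence intervals. A reader who relies on the stated 80% power could then give a non-significant result more weight against the intervention than the design supports.

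**Working it through.** **1. Reproducing the plan's figure.** Inputs from the Statistical power section: p1 = 0.80, p2 = 0.60 (20% read as percentage points), alpha 0.05, power 0.80. Two-sided testing is my assumption. With the pooled formula and mean proportion 0.70:

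n = [1.960 × √(2 × 0.70 × 0.30) + 0.842 × √(0.80 × 0.20 + 0.60 × 0.40)]² / 0.20² = (1.2702 + 0.5323)² / 0.04 = 81.2, so 82 per group and 164 in total.

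This matches exactly with no design effect. Other unclustered variants for 80% versus 60% do not match: unpooled 79, arcsine 81, continuity-corrected 91, one-sided 64. A 20% relative reduction (80% to 64%) gives 123.

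**2. Applying the stated ICC.** Design effect DE = 1 + (m − 1) × 0.05, where m is workers per unit.

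| m | DE | n per group = 81.2 × DE |
|---|---|---|
| 20 | 1.95 | 158.4 |
| 40 | 2.95 | 239.6 |
| 60 | 3.95 | 320.8 |

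The need is therefore about 160 to 320 per group. Over units of 20 to 60, the smallest clustered figure from any pooled variant tried, with or without continuity correction, is 125 per group (one-sided, m = 20). The matching two-sided formula returns 82 only if m = 1.

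**3. Power for a follow-up comparison of two proportions.** I assume four equal units per arm. Effective n per arm is 4m / DE. The normal figure uses the pooled formula. The t figure uses a noncentral t on 8 − 2 = 6 df with noncentrality 0.20 / √(0.40 / effective n).

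| m | Workers in total | Effective n per arm | Power, normal | Power, t on 6 df |
|---|---|---|---|---|
| 20.5 | 164 | 82 / 1.975 = 41.5 | 51% | 40% |
| 40 | 320 | 160 / 2.95 = 54.2 | 63% | 50% |
| 60 | 480 | 240 / 3.95 = 60.8 | 68% | 54% |
| no limit | – | 4 / 0.05 = 80 | 79% | 66% |

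The last row is a ceiling. Effective n cannot exceed 80 per arm and 81.2 is needed, so this comparison cannot reach 80% with four units per arm at ICC 0.05.

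**4. Power for the planned contrast.** I approximate it by a t test on the eight unit-level changes from baseline. For a unit with baseline and follow-up standard deviations s0 and s1 (s² = p(1 − p)), the variance of its change is

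(s0² + s1²)(0.05 + 0.95/m) − 2 s0 s1 (0.05c + 0.95r/m),

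where c is the cluster autocorrelation and r the within-person correlation. The article gives neither; I take c from 0.5 to 1 and r from 0 to 0.5. The control arm is held at 80% and the intervention arm falls from 80% to 60%.

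Example at m = 20.5, c = 0.5, r = 0: the variances are 0.0287 (intervention) and 0.0228 (control). SE = √((0.0287 + 0.0228) / 4) = 0.1135, noncentrality 0.20 / 0.1135 = 1.76, power 32%.

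| m | r = 0, c from 0.5 to 1 | r = 0.5, c from 0.5 to 1 |
|---|---|---|
| 20.5 | 32% to 45% | 44% to 72% |
| 60 | 50% to 86% | 58% to 99% |

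**The case against.** The best defence leaves the arithmetic alone and disputes what follows from it. Four parts deserve an answer.

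- *The sample is a minimum.* The article calls 164 a minimum, and eight units of 20 to 60 workers hold 160 to 480. This stands: the 40% to 51% figure belongs to 164 workers only.
- *The split is not fixed.* Four units per arm is an assumption. This stands, though an unequal split would generally cost power.
- *The planned analysis is a different one.* Data analysis compares changes from baseline, not follow-up prevalences. This stands and matters most. With large units and a high cluster autocorrelation, eight units can exceed 80% power. A reader might infer that the trial's true power is 40% to 51%, or that eight units reach 80% only if prevalence falls to about 47% to 52%. Both hold only for the follow-up comparison, and the article does not support either for the planned contrast. Equally, the change contrast does not rescue the stated calculation: the section does not invoke it and gives no correlation for it, and at 164 workers none of the assumed values reaches 80%.
- *The effect is recoverable.* Because 82 matches 20 percentage points exactly, the relative reading (80% to 64%) is evidently not what was calculated. This stands; one clarifying word settles it.

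The article also warns, under Methodological considerations, that unlinked questionnaires could limit power. That is a separate reason and does not correct the sample size sentence. Nor is this a detail that an article leaves to a fuller document: inputs are listed, said to be applied, and followed by a result they do not give.

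**Conclusion.** The point holds as an arithmetic error. The stated 82 per group is the individually randomised number for 80% versus 60%. With the listed ICC and unit sizes, the same formula gives about 160 to 320 per group, roughly two to four times as many. That the design effect was left out is inferred from the exact match; whatever the cause, the listed inputs do not give the stated output.

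The size of the power shortfall is conditional. For a follow-up comparison with four units per arm, power runs from 51% (normal) or 40% (t) at 164 workers to 68% or 54% at 60 per unit, with a ceiling of 79% or 66%. For the planned change-from-baseline contrast on 6 df, it is about 32% to 72% at 164 workers and about 50% to 99% at 60 per unit, under the assumed correlations. The documents therefore support neither the claim that 164 workers give 80% power at ICC 0.05 nor a claim that eight units can never do so.

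**What to change.** Correct the Statistical power section as follows.

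1. State that 82 per group (164 in total) is the unclustered number for an absolute fall from 80% to 60%, two-sided alpha 0.05, power 0.80. Withdraw the claim that 164 subjects give 80% power at ICC 0.05.
2. Restate power for eight units as a conditional range. Give the follow-up comparison figures (normal / t on 6 df): 51% / 40% at 164 workers, 63% / 50% at 40 per unit, 68% / 54% at 60 per unit. State the four-to-four split and the workers per unit as assumptions.
3. Add that power for the planned change-from-baseline contrast depends on the cluster autocorrelation and the within-person correlation. Give the range with the values assumed: about 32% to 72% at 164 workers and 50% to 99% at 60 per unit, for autocorrelation 0.5 to 1 and within-person correlation 0 to 0.5.
4. Do not add an unconditional statement of the smallest effect detectable with 80% power.
5. Commit to interpreting a non-significant result through its confidence interval, not as evidence of no effect.

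The cost is a rewritten paragraph and a less favourable stated power. The units are already randomised, and no extra workers or units are needed.
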